## Statistical Analysis

***Exploratory analysis***

Before the data will be further analysed, all data sets will be cleaned. The demographic data of the participants will be presented in a table, describing gender, age, education, and medical history of each participant. For each variable at each time point group data in the form of the range, median, mean, and standard deviation will be tabulated, frequency distributions plotted and examined, and missing or anomalous data points investigated. Missing data will be handled following the ‘last observation carried forward’ method. Correlations between measures within and across time points will be examined to assess consistency (within time) and predictability (across time and measures) of responding.

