3. Study period 3: The intervention in group 1 will be withdrawn for four weeks (OFF-phase), whereas group 2 starts taking the Lightning Stiks^TM^ (ON-phase). Both groups answer the same questionnaires as before every two weeks.
4. Study period 4: Group 2 stops taking the interventions (OFF-phase) whereas group 1 starts taking them for another 12 weeks (ON-phase). Both groups answer the same questionnaires as before every two weeks.
5. Study period 5: When Group 1 has been taking the Lightning Stiks^TM^ for four weeks, Group 2 starts taking the multinutrient intervention for another 12 weeks and will answer questionnaires every two weeks.

Every four weeks, the children’s parents and children will meet with the study coordinator at *Te Puna Toiora* to complete various psychometric questionnaires assessing their children’s behaviour, including hyperactivity/impulsivity, inattention, emotion dysregulation, irritability, sleep, social relationships, diet, and side effects. If participants cannot be met in person, the meeting will be held via Zoom. Both the child and the parent will answer the questions of the Measure it Yourself Medical Outcome Profile (MYMOP) (see below) jointly; otherwise, they will answer the questionnaires on their children’s or their own behalf. In addition, questionnaires assessing emotion dysregulation and irritability will also be emailed to another adult who is close to the child, such as a grandparent, aunts/uncles, or teachers, twice over the period whole study period. Please find a diagram with all study phases below.

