#### **Participant recruitment**

Participants will be recruited nationally across New Zealand, mainly by self-referrals following online advertisement on social media. Specifically, recruitment will take place through advertisement on Facebook (via the Mental Health and Nutrition Research Lab Te Puna Toiora account, the University of Canterbury Student Association (USCA) noticeboard), and Instagram (via the Te Puna Toiora account). Further, advertisement posters and brochures will be distributed around the UC campus, with local General Practitioners and mental health service providers. To increase Māori participation in the study, efforts will be made to engage with Māori service providers.

*Sample size*

Forty participants will be sought for the study, split 20:20 between group 1 and 2 . This number of participants is considered a sufficient sample size to determine whether the Lightning Stiks^TM^ are successful in reducing emotion dysregulation with sufficient power. This is a reasonable expectation as it allows for an adequate number of successful replications between participants, following the What Works Clearinghouse Standards for single-case designs (Handbook, n.d.).

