### Assessment Tools

An on-line survey created with Qualtrics will ask the participants and their parents to complete measures of emotion dysregulation, irritability, inattention, hyperactivity/impulsivity, diet, sleep, depression, anxiety and stress. The measures that are proposed in this study are standard measures used in clinical trials. In addition, the study coordinator will meet with the participants once a month in person at Te Puna Toiora to collect data on emotion dysregulation, mood, side effects, and interpersonal skills. If participants cannot be met in person, these meetings will be held via Zoom or other online platforms.

Primary outcome measures

*Clinician-administered:*

*The Clinician Affective Reactivity Index (Parent/Child Interview Guide) (CL-ARI):* This scale is a parent-report measure that assesses emotion regulation and irritability in children over the past week, looking at temper outbursts and irritable mood, and their frequency, severity, and duration. Further, it assesses whether the child’s irritable behaviour causes problems in the family, impairments in school, and assesses potential improvements over time. The CL-ARI has good internal consistency (*α* = .89) and adequate test-retest reliability (*ICC* = .67) (Haller et al., 2020). In the proposed study, the study coordinator will meet the parent and the child every four weeks to collect data on the CL-ARI in person.

*Clinical Global Impressions - Improvement Scale (CGI-I) (Guy, 1976):* The CGI-I is a clinician-administered scale that rates, based on all information obtained from all raters (parents, child and significant other) how much better/worse the participant is functioning since baseline across irritability/emotion dysregulation, mood, stress, energy, and sleep. Each item has seven responses, ranging from “very much improved” (1) to “very much worse” (7) and helps to provide a brief, overall assessment of the participant. The CGI-I is not used during baseline assessment. The CGI-I has demonstrated high external validity (*r* = 0.74) (Kadouri et al., 2007) and is widely used in clinical trials.

Secondary outcome measures

*Clinician-administered:*

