***Nomothetic analysis***

The ideographic analysis described above will be complemented by nomothetic analyses, which will involve hierarchical linear modeling. Baseline demographic variables will be examined using multiple regression and discriminant function analysis to determine if there are predictors of response to treatment.

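### LOCF has no limit at phase changes, so a CL-ARI missed in the switching phases is usually filled from the opposite treatment state, which pulls H2 to H5 toward no effect

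*Protocol*

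**What the plan says.** The Exploratory analysis paragraph of the protocol's Statistical Analysis section opens with data preparation: "Before the data will be further analysed, all data sets will be cleaned". It then sets the rule: "Missing data will be handled following the ‘last observation carried forward’ method". No within-phase limit, alternative method or sensitivity analysis follows.

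Under Study design, the groups swap states at each boundary of periods 2 to 4. For period 3: "The intervention in group 1 will be withdrawn for four weeks (OFF-phase), whereas group 2 starts taking the" product. Group 1 is ON, OFF, then ON for 12 weeks. Group 2 is OFF, ON, OFF, then ON for 12 weeks.

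For the primary CL-ARI, Assessment Tools says that "the study coordinator will meet the parent and the child every four weeks to collect data on the CL-ARI in person", and Appendix B agrees. Appendix B lists CGI-I, ARI, SDQ and CSHQ at weeks 2 and 4 of phases 2 and 3.

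H2 predicts benefit while ON and its loss while OFF. H3, H4 and H5 compare the groups in months 1, 2 and 3, when one is ON and the other OFF. The Nomothetic analysis adds group-level analyses, "which will involve hierarchical linear modeling".

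**The concern.** In periods 2 to 4 each four-week phase holds one CL-ARI value. If it is missed, no earlier value exists in that phase, so LOCF reaches back across a treatment switch. The filled score then says that nothing changed when the product was started or stopped, which is the very thing that H2 to H5 test.

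The trial is open-label with no placebo, so the reversals and the staggered group contrasts are its main evidence. A rule that writes no change into them weakens that evidence in proportion to the missing rate. It also feeds Cohen's d, the common language effect size, the modified Brinley plots and any responder label given at the end of a phase.

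**Working it through.** **Is there a figure to reproduce?** No. The protocol gives no missing or dropout rate. Its sample size of 40 comes without alpha, power, effect size or SD. The check is therefore the effect of the stated rule over a range of m.

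**Which visits cross a switch.** For a single missed visit with the preceding one observed:

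| Group | Opposite state | Same state |
|---|---|---|
| 1 (weeks 4 to 20) | 4, 8, 12 | 16, 20 |
| 2 (weeks 4 to 24) | 8, 12, 16 | 4, 20, 24 |

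That is 3 + 3 = 6 of 5 + 6 = 11 visits.

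**Share of the effect retained.** Assumptions: baseline is complete; each later visit is missed independently with probability m in both groups; the effect τ is fully present at the end of an ON phase and fully gone at the end of an OFF phase; there is no time trend.

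- H3, week 4. Group 1 keeps (1−m)τ, because missed values take the OFF baseline. Group 2's fills are OFF into OFF and do no harm. Difference: (1−m)τ.
- H4, week 8. Group 2 (ON) shows (1−m)τ. Group 1 (OFF) shows m(1−m)τ, from children seen at week 4 but not week 8. Difference: (1−m)τ − m(1−m)τ = (1−m)²τ.
- H2, group 1 ON to OFF. The mean effect goes from (1−m)τ at week 4 to m(1−m)τ at week 8. Change: (1−m)²τ.
- H5, week 12. Group 1 (ON) shows (1−m)τ + m²(1−m)τ; the second term is children last seen at week 4, also ON. Group 2 (OFF) shows m(1−m)τ. Difference: (1−m)(1−m+m²)τ.

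| m | H3 | H4 and H2 | H5 |
|---|---|---|---|
| 2% | 98% | 96% | 96% |
| 5% | 95% | 90% | 90% |
| 10% | 90% | 81% | 82% |
| 20% | 80% | 64% | 67% |

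**Simulation.** 5,000 runs, 20 per group, assumed effect 0.60 SD, within-child correlation 0.67 (borrowed from the CL-ARI test-retest ICC). Neither value is a planning assumption of the protocol. At m = 20% the LOCF estimates were H3 0.48, H4 0.39, H5 0.40 and H2 0.39, in line with the formulas. Observed data gave 0.60 to 0.61. With permanent dropout in place of isolated misses, H4 fell to 0.425 at 10% per visit and 0.29 at 20%.

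A random-intercept model over six visits with m = 20% (250 runs) gave 0.41 under LOCF and 0.59 on observed visits.

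**Intervals at m = 20%.**

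| Contrast | SE, LOCF | SE, observed | 95% CI coverage, LOCF | Coverage, observed |
|---|---|---|---|---|
| H3 | 0.318 | 0.352 | 94% | 95% |
| H4 | 0.322 | 0.353 | 91% | 95% |
| H5 | 0.322 | 0.352 | 92% | 95% |
| H2 change | 0.173 | 0.224 | 75% | 93% |
| Hierarchical model | 0.109 | 0.124 | 56% | 94% |

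The LOCF SE is close to that estimator's own sampling SD for H2 (0.173 against 0.178) and exceeds it in the model (0.109 against 0.095). The lost coverage is therefore mostly bias.

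**Two-weekly measures.** A missed week 4 is filled from week 2 of the same phase if that was seen. The switch is crossed only when both are missed, so the week-4 loss in H4 is about 2m²: 2 × 0.2² = 8% at m = 20%. A missed week 2 is filled across the switch.

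**The case against.** The strongest defence has five parts.

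- **Placement.** The sentence sits under exploratory analysis and might govern only the descriptive tables. But it belongs to data preparation that precedes further analysis, and no other missing-data rule exists for the model.
- **Scope.** A reader might infer that almost every carried CL-ARI comes from the wrong state, or that every imputed pair in H4 and H5 is reversed. The design does not support either. The final 12-week ON phase has same-state fills, and a child who misses two consecutive visits can be given a right-state score. H3 is affected in group 1 only. CGI-I, the other primary outcome, and ARI, SDQ and CSHQ are much less exposed at week 4. These limits stand.
- **Size.** Meetings can be held online, so few may be missed. At 2 to 5% missing, H4 keeps 96 to 90% of the effect. This stands too.
- **Direction.** Under random missingness the bias hides a benefit and does not create one. But the Ethics section discontinues children who come to need psychiatric medication and allows withdrawal when symptoms worsen, so response-related missingness is foreseeable. The direction is then not known.
- **Role of the model.** The study calls itself explorative, and the hierarchical model complements the individual-level analysis. That does not protect the individual-level results: a copied score appears there as no change across a switch.

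A fair caution also applies to the remedy. Analysing observed pairs alone could inflate the effect if non-responders leave.

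**Conclusion.** The point holds for the CL-ARI in the switching phases. Unrestricted LOCF usually fills a value missed there from the opposite state and shrinks H2, H4 and H5 by about 18 to 19% at 10% missing and 33 to 36% at 20%. H3 shrinks by 10% and 20%. These shares do not depend on the effect size or the within-child correlation. They do rest on the assumed missing rate, on misses independent of response, and on an effect that appears and disappears fully within each phase.

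A reader might infer that too-narrow intervals are a problem of equal weight. They are narrower than the observed data support, because copied values count as observed, but bias accounts for most of the lost coverage. A reader might also infer that LOCF flattens the duration effect in H9; no calculation here supports a figure for that. The likely damage ranges from slight to substantial with a missing rate that the protocol does not state. The rule is still unsuited to this design at any rate.

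**What to change.** - Delete the LOCF sentence.
- Fit the planned hierarchical model by (restricted) maximum likelihood to all observed visits, and state the missing-at-random assumption.
- Compute d and its interval, the common language effect size and the Brinley plots from observed values, and report the number of pairs behind each.
- Do not carry a value across a phase change.
- Add a sensitivity analysis for dropout related to response, since neither the model nor the observed pairs protect against it.

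No extra data are needed. The cost is a short rewrite of the missing-data text, a little more analysis work, and slightly wider intervals (at 20% missing, a model SE of 0.124 instead of 0.109 in the simulation).

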***Ideographic analysis***

Graphical procedures such as spaghetti plots will be used to examine consistency of individual response over time within the study phases (where there are multiple time points). Modified Brinley Plots (Blampied, 2017) will examine the consistency of patterns of response to treatment and replications of such patterns over study phases. Sigma Plot will be used to examine individual change across time in the context of all other participants’ scores at that time, along with measures of means and SDs. In addition, effect sizes (ES), namely Cohen’s *d,* the 95%CI on *d*, and the Common Language ES (CLES; Lakens, 2013) will be reported. This gives the probability, expressed as a %, that a randomly selected participant will have an improved score at the second measurement point relative to the first measurement. Lakens (2013) software will be used to calculate the CLES and ESCI (Cumming, 2012) to compute *d* and the CI.

The ideographic analysis will also use single-case visual analysis to examine the extent to which there is replication of treatment effects across individuals and replicated phases. Note that the design means that the initial phases for the two groups will permit detection of any initial treatment effect for those in group 1 period 2 relative to those in group 2 period 2. The respective transitions into respectively group 1 period 3 and group 2 period 3 will permit observation of (a) any loss of therapy effect for group 1 changes in therapeutic direction (going ON to OFF) and any changes in the therapeutic direction for group 2 (going OFF to ON). Subsequent phase changes will permit observation of any replication of these effects, with the possibility of accumulation of therapy effects across phases as observed by Gordon et al. (2015).

Consistency analysis will examine consistency of individual response across primary outcome measures, i.e., to establish if an individual with a clinical level of response on any one DV will also have displayed similar positive responses on other DVs. Also, at the end of each treatment phase, participants may be classified using primary outcome measures as ‘Responders’ and ‘Non-responders’.

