# Method

## Study design

The proposed study will use a two-arm withdrawal open-label design, following the advice of Hersen and Barlow (1976) on how to evaluate the effect of drug interventions on behaviour using a single-case approach. In particular, the study will have two groups, and participants will be randomized in equal numbers to either group 1 or group 2 by means of a randomized block procedure.

There will be five study phases:

1. Study period 1: Online screening and baseline assessment: Participant children will be screened for eligibility (see below) by providing information regarding their demographics as well as completing measures assessing emotion dysregulation and irritability. If they are eligible, they and their parent(s) will meet with the study coordinator [name] at Te Puna Toiora during the week before the intervention period starts. During that meeting, eligibility will be checked, questions about the research answered, consent obtained, and the participant will complete a baseline assessment. In case the participants cannot be met in person (e.g., due to COVID-19 or because they live outside of Christchurch), meetings will be held and consent conducted over the phone or online (via Skype/Facetime/Whatsapp/Zoom). Consent forms can be uploaded and emailed/mailed back to Te Puna Toiora. Once consent is given, baseline data will be collected by means of an online survey (Qualtrics) including various psychometric measures (see below). Participants in group 1 will be given one month’s supply of Lightning Stiks^TM^ immediately after the baseline assessment. If participants cannot be seen face-to-face, the Lightning Stiks^TM^ will be delivered by courier. Those randomised to group 2 will have a delayed 4 week start (see Figure 1)
2. Study period 2: Group 1 will start taking the intervention for 4 weeks (ON-phase). Every two weeks, the parents will fill out various psychometric questionnaires assessing their children’s emotion dysregulation and irritability (see measures below), other symptoms linked to ADHD, sleep, diet, mood, anxiety and stress. Group 2 will be in a delayed baseline phase during study period 1, but will be monitored by answering the same psychometric questionnaires as group 1 every two weeks.

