#### Inclusion Criteria:

1) Participants must be between 5 and 10 years of age, 2) able to ingest 1 Lightning Stik^TM^/day), 3) the children’s parents need to have English language competence sufficient to understand study materials to answer questionnaires, 4) the children need to have English language competence sufficient to understand and answer the questions asked in the child-related measure, 5) participants need to have at least mild-to-moderate levels of emotional dysregulation and irritability following the Affective-Reactivity-Index (ARI), represented by a total score of 3 or higher.

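### The CLES is defined pre-post, Cohen's d has no stated contrast, and no effect estimate is named for the randomised week-4 comparison with untreated children

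*Protocol*

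**What the plan says.** The Study design section sets out an open-label trial: "The proposed study will use a two-arm withdrawal open-label design". Allocation is random: "participants will be randomized in equal numbers to either group 1 or group 2 by means of a randomized block procedure". In study period 2, group 1 takes the product for four weeks. Group 2 waits, but "will be monitored by answering the same psychometric questionnaires as group 1 every two weeks". Hypothesis 3 is a between-group statement about that month, and hypotheses 4 and 5 are between-group statements about the next two.

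Under Ideographic analysis the protocol will report Cohen's d with its 95% CI, and the CLES. The CLES is explained as the probability "that a randomly selected participant will have an improved score at the second measurement point relative to the first measurement". No contrast is given for d. The same section provides that "at the end of each treatment phase, participants may be classified using primary outcome measures as" responders or non-responders. It gives no threshold and no matching classification of untreated children. One of the primary measures, the CGI-I, is itself rated as change since baseline.

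That section also notes that the first phases allow an effect in group 1 to be seen relative to group 2 in period 2, but it does so while describing single-case visual analysis. Nomothetic analysis adds hierarchical linear modelling without naming a contrast. Appendix B schedules the CL-ARI at baseline and at week 4 of phase 2, and the CGI-I at weeks 2 and 4 of phase 2, in both groups.

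**The concern.** A pre-post effect size credits the product with whatever would have happened anyway. Children enter on a raised parent-rated irritability score, "represented by a total score of 3 or higher", in an open-label study. Some improvement between two visits is to be expected from the passage of time and from regression to the mean.

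Responder status has the same weakness when it is assigned only at the end of treatment phases. For group 2 at the end of period 3, a CGI-I rating of change since baseline also covers the four untreated weeks of period 2.

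The design contains a remedy that the named summaries do not use. In period 2 a randomised group is untreated and has never been exposed. From period 3 onward one or both groups have already taken the product, and the protocol itself anticipates that effects may accumulate across phases. Period 2 is therefore the only randomised contrast free of carry-over, and the protocol names neither a between-group effect size nor a responder difference for it. The summaries with a clear interpretation would then be those least able to separate the product from natural change.

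**Working it through.** The protocol gives no effect-size calculation to reproduce. The check asks how far the stated CLES moves with no product effect, and what the randomised contrast would give instead.

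**Inputs**
- Pre-post correlation r = 0.67. This is the CL-ARI test-retest ICC from Assessment Tools, used as a stand-in.
- Natural improvement of 0.2, 0.3 or 0.4 SD. This is an assumption; the protocol gives no figure.
- Group size from the Sample size text: "Forty participants will be sought for the study, split 20:20 between group 1 and 2".

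**Step 1: CLES with zero product effect.** For paired normal scores of equal variance, CLES = Φ(δ / √(2(1 − r))), where δ is the mean improvement in SD units. Here √(2 × 0.33) = 0.812.

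| Assumed natural improvement δ | δ / 0.812 | CLES |
|---|---|---|
| 0 | 0 | 50% |
| 0.2 | 0.246 | 60% |
| 0.3 | 0.369 | 64% |
| 0.4 | 0.492 | 69% |

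A pre-post d would equal δ itself.

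**Step 2: the randomised contrast under the same conditions.** Natural change has the same expectation in both groups, so the expected between-group d is 0 and the between-group CLES, Φ(d / √2), is 50%.

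**Step 3: what that contrast does not remove.** Suppose natural change is 0.3 SD and children known to be taking the product gain a further 0.2 to 0.4 SD from expectancy (both assumed), again with no product effect. The pre-post d is 0.3 + 0.2 = 0.5 to 0.3 + 0.4 = 0.7. The between-group d is still 0.2 to 0.4, because group 2 knows that it is untreated.

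**Step 4: precision at 20 per group.** The 95% half-width on unadjusted d is 1.96 × √(2/20 + d²/80).
- At d = 0: 1.96 × 0.316 = 0.62.
- At d = 0.66 (the emotional dysregulation result in the child RCT cited in Background): 1.96 × 0.325 = 0.64.

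**Step 5: gain from baseline adjustment.** The variance ratio is 1 / (1 − r²). At r = 0.5 it is 1 / 0.75 = 1.33; at r = 0.67 it is 1 / 0.551 = 1.81. At d = 0.54 (the emotion regulation and irritability result in the cited student trial of the same product), two-sided 5% power is 40% unadjusted and 63% adjusted with r = 0.67.

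**Step 6: responder difference, for illustration.** If the rates were the 47% and 28% of the cited child RCT, the 95% half-width would be 1.96 × √(0.47 × 0.53/20 + 0.28 × 0.72/20) = 1.96 × 0.150 = 29 percentage points, and power would be 23%.

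**The case against.** The strongest reply is that the plan as a whole is controlled. It follows single-case methodology, in which control comes from staggered starts, ON/OFF reversals and replication. Hypotheses 3 to 5 are between-group, and the hierarchical model could deliver exactly the contrast asked for. Its terms are commonly left to a statistical analysis plan, which is not to hand. This stands. A reader might infer that the trial is uncontrolled, or that the randomised comparison will have no effect estimate. The protocol supports neither. What it supports is that the one effect size it defines is pre-post, and that it names no between-group estimate.

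Three other strong readings also go too far:

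- **That d is a pre-post measure in treated children.** The pre-post sentence describes the CLES only. For d the contrast is simply unstated, and nothing limits either measure to treated children or ON phases.
- **That effectiveness will be judged on responder rates.** Classification is optional and has no threshold, and no section makes a responder rate the test of hypothesis 1.
- **That about 60% (28/47) of a treated-only responder rate is non-specific and would be removed by comparing with group 2.** The 28% in the cited child RCT is a blinded placebo response and includes expectancy, which an open-label untreated group does not reproduce. That trial also enrolled children with ADHD aged 7 to 12.

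Finally, regression to the mean on the CL-ARI is indirect. Selection is on the screening ARI, a different scale, and the CL-ARI baseline is taken later. Its size cannot be derived from the protocol, so the shifts above are a range and not an estimate.

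**Conclusion.** The point holds in a limited form. The CLES as defined, and responder status if assigned only at the end of treatment phases, absorb natural change and regression to the mean. For d the fault is an unstated contrast. Under an assumed natural improvement of 0.2 to 0.4 SD, with r = 0.67 standing in for the pre-post correlation, the CLES would read 60% to 69% with no product effect.

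A baseline-adjusted week-4 contrast between the randomised groups is a better main estimate and uses data already scheduled. It has two limits. It does not remove expectancy, and it is imprecise: the half-width on unadjusted d is about 0.62 to 0.64. That imprecision is a reason to report the interval rather than to omit the contrast.

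**What to change.** In Statistical Analysis, specify the following.

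1. **Main effect estimate.** The difference between group 1 and group 2 in CL-ARI at week 4 (end of period 2), adjusted for baseline CL-ARI by ANCOVA or the equivalent term in the hierarchical model. Report it with d, its 95% CI and a between-group CLES (the chance that a randomly chosen group 1 child fares better than a randomly chosen group 2 child).
2. **Responders.** Where children are classified, apply the same rule to untreated group 2 at week 4, and report the difference in proportions with its CI.
3. **Descriptive figures.** Label pre-post d and CLES as descriptive. Give the same label to any responder figures from OFF phases, which are open to carry-over.
4. **Limits.** State that, because the trial is open-label, the week-4 contrast removes natural change and regression to the mean but not expectancy, and that it is imprecise at 20 per group.

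The cost is analysis wording only. Appendix B already schedules the CL-ARI at baseline and week 4, and the CGI-I at week 4, in both groups. Where natural improvement occurs, the main figures will be smaller than the pre-post ones.
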